### Blinding

The control arm receives sham stimulations that will be applied in a way that is indistinguishable from active stimulation, i.e., in the same time-schedule of intervention and at identical localizations.

For all data transfers between the trial site and the cloud, the EDSM—Energy and Data Storage Module is used as an integral component of the neuroConn DC-STIMULATOR MOBILE. The data transmitted via cloud, e.g., the technical data required for stimulation, cannot be changed by trial site. Thus, the blinding is guaranteed.

### Concomitant treatment

All medications that are approved according the guidelines for the treatment of adult ADHD in Germany are permitted as additional treatment during study participation. Other psychotropic medication is not allowed (i.e., benzodiazepines, z-hypnotics, antidepressants, neuroleptics). If present, the pharmacological therapy should be stable within the last 3 months before randomization and should be kept constant until assessment of the primary endpoint. Critical changes within the treatment period lead to exclusion from per-protocol analysis. Changes in medication and non-pharmacological treatments are continuously registered.

## Study endpoints

### Primary outcome measure

Primary objective is to test the hypothesis whether or not tDCS is effective in reducing ADHD symptoms with a benefit for at least 2 weeks after the end of stimulation and superior to sham stimulation determined by DSM-IV ADHD symptoms total score (DSM-ADHS) of the CAARS-S-SR. Potential lasting effects of active and sham stimulation will be monitored for 90 days p.i.

### Secondary outcome measures

As secondary endpoints, the following scores and safety assessments will be compared between active and sham stimulation:CAARS-S-SR DSM-IV scales: inattentive symptoms (DSM-IN) and hyperactive-impulsive symptoms (DSM-HY/I) on visit 1, 5, and all follow-up visits (6–10)Assessment of Reaction time, variability, omission, and action errors by CPT on visit 1, 5, 7, and 10ADHD-specific quality of life assessed by AAQoL on visit 1, 5, and all follow-up visitsSymptomatic distress assessed by SCL-90-S on visit 1, 5, and all follow-up visitsSleep quality and disturbance assessed by PSQI on visit 1, 5, and all follow-up visitsBDI-II before first and after last tDCS application and on all follow-up visits CRQ after each tDCS applicationIncidences of adverse clinically relevant findings

### Sample size calculation

The estimation of the requested sample size in Stim-ADHD was based on various data from our own former, in parts unpublished, research activities and studies. According to our pre-/post-data, moderate to high correlations between baseline and post-treatment data of *r* ≈ 0.39… > 0.7 were observed in previous populations, with lower values in pharmacotherapy, and *r* = 0.57 in the aggregated dataset. Because of the rather small samples and since no valid assumption can be made on the impact of the further stratification criteria on pre-/post-correlation, we conservatively chose *r* ≈ 0.5 for calculation of sample size.

PASS sample size software (http://www.ncss.com/software/pass/pass-documentation; version 14, 2016) was used, based on an ANCOVA design with baseline CAARS DSM-IV and the stratification criteria as covariates, means as reported and *R*^2^ = 0.25.

With a significance level of *α* = 5%, a randomization ratio 1:1, and 208 patients in total, a power of 81% will be reached to detect between-group differences of 3.5 points (assuming a small sham effect and/or regression to the mean in our control group as well as to be conservative in our assumptions).

The effect size of this design is determined by *f* = SD_group means_/SD SD_CAARS DSM-IV ADHD total post_ = 0.172. According to Cohen [49], *f* < 0.1 is regarded as small, *f *≈ 0.25 as moderate. With less conservative (but reasoned) assumptions on higher *R*^2^ (see observed pre–post-correlation) and lower SD_post_ (due to a rather homogeneous population and standardized intervention), and with possibly lower dropouts (because of the non-pharmacological intervention as seen in our patients), the power would increase and possibly smaller effect sizes may be detectable.

### Statistical analysis

The full analysis set [FAS, based on the intention-to-treat (ITT) strategy] contains all randomized patients with informed consent and (at least) a single study intervention performed. The per-protocol (PPS) comprises all patients belonging to the FAS without major protocol violations. To identify between-groups differences for the primary endpoint, an ANCOVA with treatment (tDCS vs. sham stimulation) as main factor and CAARS DSM-IV ADHD total at randomization, ADHD sub-type and pre-medication (stratification criteria) as covariates within the FAS will be performed.

If a significant between-groups difference is identified in the primary analysis, a linear mixed model (LMM) for repeated measurements will be applied to analyze the course of CAARS DSM-IV ADHD total, including 5 assessments per patient: at baseline, at days 14, 28, 56, and 90 post-intervention. For sensitivity analysis, multiple missing value (MV) imputations may be performed to support the results of the repeated measurements LMM and investigate the influence of MVs. No α adjustment for multiple testing is required. (Quasi-)metric secondary and safety endpoints will be analyzed analogously to the primary endpoint.

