## Abstract

Transcranial direct current stimulation (tDCS) is a non-invasive brain stimulation treatment used as an alternative or complementary treatment for various neuropsychiatric disorders, and could be an alternative or add-on therapy to psychostimulants in attention-deficit hyperactivity disorder (ADHD). Previous studies provided some evidence for improvements in cognition and clinical symptoms in pediatric and adult ADHD patients. However, data from multi-center randomized controlled trials (RCTs) for this condition are lacking. Thus, our aim is to evaluate short- and mid-term effects of tDCS in this multi-center, randomized, double blind, and sham-controlled, parallel group clinical trial with a 1:1 randomization ratio. Primary endpoint is the total score of DSM-IV scale of the internationally established Conners’ Adult ADHD Rating Scales (German self-report screening version, CAARS-S-SR), at day 14 post-intervention (p.i.) to detect short-term lasting effects analyzed via analyses of covariance (ANCOVAs). In case of significant between-groups differences at day 14 p.i., hierarchically ordered hypotheses on mid-term lasting effects will be investigated by linear mixed models with visit (5 time points), treatment, treatment by visit interaction, and covariates as fixed categorical effects plus a patient-specific visit random effect, using an unstructured covariance structure to model the residual within-patient errors. Positive results of this clinical trial will expand the treatment options for adult ADHD patients with tDCS and provide an alternative or add-on therapy to psychostimulants with a low risk for side effects.

*Trial Registration* The trial was registered on July 29, 2022 in the German Clinical Trials Register (DRKS00028148).

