### Safety aspects and data safety monitoring board

The exclusion criteria of this trial include all contraindications for the application of tDCS (e.g., metal plates or electronic implants in the brain or skull, skull defects, history of epileptic seizures, cardiac pacemaker). In addition, major depressive disorder (MDD) severity and suicide risk will be measured during treatment and follow-up visits with the BDI-II due to the theoretical risk of worsening or new development of depressive symptoms. This risk arises as the electrode placement in our study is opposite to the usual placement in depression treatment.

Information on adverse events (AEs) and serious adverse events (SAEs) will be collected during treatment period and up to the first follow-up visit after treatment period. (S)AE will be followed up until complete recovery and/or patient’s status is stable. A Data Monitoring Committee (DMC), consisting of three independent experts without conflicts of interest, will meet periodically to perform a review of the accumulated study data regarding the safety of the trial intervention as well as the integrity and validity of the data.

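### A significant day-14 test decides whether the CAARS DSM-IV total is compared between arms at days 28, 56 and 90 at all, not only whether that comparison is confirmatory

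*Protocol article*

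**What the plan says.** Under Statistical analysis, the primary test is an ANCOVA of the day-14 CAARS DSM-IV total. The next step is conditional: "If a significant between-groups difference is identified in the primary analysis, a linear mixed model (LMM) for repeated measurements will be applied". That model covers the CAARS total only, at baseline and days 14, 28, 56 and 90.

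The Abstract makes the same step depend on a significant day-14 difference and presents it as a testing hierarchy: "hierarchically ordered hypotheses on mid-term lasting effects will be investigated by linear mixed models".

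A separate, later sentence under Statistical analysis deals with the other scales: "secondary and safety endpoints will be analyzed analogously to the primary endpoint". It carries no condition. The Secondary outcome measures section lists, also without condition, the scales to be compared between arms. The list includes the two CAARS DSM-IV subscales and the BDI-II at all follow-up visits. It does not include the CAARS DSM-IV total.

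**The concern.** A fixed sequence protects the type I error by limiting which results may be claimed. It does not require the later model to be left unfitted. Here the condition attaches to applying the model, so a non-significant day 14 leaves the main symptom score with no planned between-arm comparison at days 28, 56 and 90.

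That sits badly with the article's own aims. The Abstract sets out to evaluate short- and mid-term effects. The Primary outcome measure section says lasting effects will be followed for 90 days. The Discussion says follow-up was extended for this purpose.

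Two things are at stake. First, the trial could collect 90 days of the total score and produce no planned estimate of the difference, even when the treatment works. Second, if mid-term estimates appear only after a significant day 14, the reported ones come from the more favourable trials. Readers and later meta-analyses would see them without their less favourable counterparts.

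**Working it through.** **Inputs from the Sample size calculation section.** The design statement is "a randomization ratio 1:1, and 208 patients in total, a power of 81% will be reached to detect between-group differences of 3.5 points", at a 5% significance level, with "means as reported and *R*^2^ = 0.25" and effect size f = 0.172. Sidedness is not stated. I take it as two-sided, which reproduces the stated power.

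**Step 1: reproduce the stated power.**
- SD = (3.5 / 2) / 0.172 = 10.17 points.
- Residual SD = 10.17 × √(1 − 0.25) = 8.81 points.
- SE of the difference with 104 per arm = 8.81 × √(2/104) = 1.22 points.
- Standardised effect δ = 3.5 / 1.22 = 2.86.
- Power ≈ Φ(2.86 − 1.96) = 81.7%. The noncentral F calculation gives 81.3%. The stated 81% is reproduced.

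**Step 2: how often the mid-term model is not run.** This is one minus the power of the day-14 test, with the SE held at 1.22.

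| True day-14 difference | Model run | Model not run |
|---|---|---|
| 3.5 points (design) | about 81–82% | about 18–19% |
| 2.5 points | 53% | 47% |
| 1.75 points (half) | 30% | 70% |
| 0 | 5% | 95% |

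**Step 3: selection of the estimates that are reported.** Given a significant result favouring tDCS, the day-14 estimate is shifted upward by SE × φ(1.96 − δ) / Φ(δ − 1.96). A later-visit estimate with the same SE and correlation ρ with the day-14 estimate is shifted by ρ times that amount. The protocol gives no correlation between post-treatment visits. I assume ρ = 0.6, which follows from a correlation of 0.7 between visits and 0.5 with baseline: (0.7 − 0.25) / (1 − 0.25) = 0.6.
- Design effect, δ = 2.86: the ratio is about 0.33. Multiplied by 0.6 this is 0.20 SE, or 0.24 points, about 7% of 3.5.
- Half the effect, δ = 1.43: the ratio is about 1.16. Multiplied by 0.6 this is 0.70 SE, or 0.85 points, about 49% of 1.75.

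Simulation over ρ = 0.5 to 0.7 gives a mean later-visit estimate of 3.70 to 3.78 against a true 3.5, and 2.46 to 2.75 against a true 1.75. The shift in points does not depend on the true later effect. The percentages do, and they assume it equals the day-14 effect.

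**The case against.** The strongest defence is that this is ordinary fixed-sequence testing in condensed form. The Abstract speaks of ordered hypotheses, and Statistical analysis says no alpha adjustment is needed, which fits a hierarchy. The article nowhere says that estimates will be withheld, and a statistical analysis plan, not shown, may provide for reporting them. The hierarchy is indeed sound, and no fault is found with it. However, both places make the modelling itself conditional. That is a stated rule, not a detail left for later, and nothing else in the article supplies the comparison for the total score.

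It is also fair that the selection effect is small at the planned effect size, rests on an assumed correlation, and becomes large only if the true effect is well below 3.5 points. That stands and limits the weight of this part.

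A reader might go further and infer that depression and other safety scores are gated too, because they are analysed in the same way as the primary endpoint. The article does not support this. The condition names only the CAARS total. The analysis of the primary endpoint is most naturally the ungated ANCOVA. The BDI-II is on the unconditional list of comparisons at all follow-up visits, and Safety aspects and data safety monitoring board says depression severity and suicide risk "will be measured during treatment and follow-up visits with the BDI-II". Nor would all mid-term efficacy information be lost, since the two CAARS subscales, quality of life, distress and sleep are on the same list. The most that can be said is that the model for these scales at the later visits is not spelled out.

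One might also infer that missing-data sensitivity work is lost when the gate closes. Multiple imputation is only optional in the article even when the gate opens, so I place no weight on that.

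**Conclusion.** The point holds for the CAARS DSM-IV total and goes no further. Followed literally, the rule leaves that score without a planned between-arm comparison at days 28, 56 and 90 in about 19% of trials at the design effect and about 70% at half of it. These figures rest on the protocol's own power inputs and a two-sided test. Halving the effect is an illustration, not a prediction.

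The upward selection of reported mid-term estimates is modest at the design effect (0.24 points) and material at half of it (0.85 points). Both figures depend on the assumed correlation of 0.6 and on equal standard errors at the two visits.

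The change should be made because it serves the trial's stated mid-term aim, but the point does not call the primary analysis into question.

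**What to change.** Replace the condition under Statistical analysis, and align the Abstract, so that:
- the repeated-measures model of the CAARS DSM-IV total is fitted whatever the day-14 result;
- between-arm differences at each modelled post-intervention visit are reported with 95% confidence intervals;
- significance at day 14 gates only the confirmatory claim for days 28, 56 and 90, taken in that fixed order. After a non-significant day 14, the later estimates are labelled descriptive.

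One further sentence could confirm that the BDI-II and the other secondary and safety comparisons lie outside the gate. If the statistical analysis plan already says all this, confirming it is enough.

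The cost is a few sentences. The 208 patients, the 81% power and the type I error stay as they are, because the order of the confirmatory tests does not change. The chance that the mid-term model is run rises from about 81% to 100% at the design effect, and from about 30% to 100% at half of it. Reporting in every case also removes the selection on day-14 significance.

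### The mid-term mixed model treats baseline CAARS as an outcome with a free treatment effect there, so its day 28, 56 and 90 contrasts forgo the precision of baseline adjustment

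*Protocol article*

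**What the plan says.** Under Statistical analysis, the primary day-14 comparison is an ANCOVA with "CAARS DSM-IV ADHD total at randomization, ADHD sub-type and pre-medication (stratification criteria) as covariates within the FAS will be performed". If it is significant, a linear mixed model for repeated measurements follows, "including 5 assessments per patient: at baseline, at days 14, 28, 56, and 90 post-intervention". The Abstract specifies "linear mixed models with visit (5 time points), treatment, treatment by visit interaction, and covariates as fixed categorical effects". It adds a random effect of visit for each patient, leaves the residual covariance unstructured, and describes the mid-term hypotheses as hierarchically ordered.

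Read together, these passages make baseline one of the five modelled responses, and both the treatment effect and its interaction with visit extend over baseline. No restriction of equal arm means at baseline is stated. The article does not list the mixed model's covariates beyond calling them categorical, and it does not name the contrast to be tested at each visit.

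The Sample size calculation section concerns an ANCOVA with baseline CAARS and the stratification criteria as covariates, r ≈ 0.5 and R² = 0.25. It reports "a power of 81% will be reached to detect between-group differences of 3.5 points" with 208 patients.

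**The concern.** Randomisation makes the true difference between arms at baseline zero. A model with an unrestricted treatment effect at baseline does not use that knowledge; it estimates the baseline difference from the data. With complete data, a separate mean for every arm and visit, and an unstructured covariance, the fitted means are simply the observed arm means. A follow-up contrast can then take only two natural forms: the raw difference at that visit, or the difference in change from baseline. Neither has the variance reduction that regression on baseline gives.

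What is at stake is the precision of the day 28, 56 and 90 results. Persistence of benefit over 90 days is a stated aim of the trial. The baseline scores that would sharpen these estimates are collected in any case.

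**Working it through.** **Inputs (Sample size calculation section).** Difference 3.5 points; f = 0.172; N = 208, allocated 1:1; α = 5%; r ≈ 0.5; R² = 0.25. The article also reports correlations from about 0.39 to above 0.7, and 0.57 in the aggregated data.

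**Follow-up SD.** It is not stated but follows from f. With two equal groups, the SD of the group means is 3.5/2 = 1.75, so SD = 1.75/0.172 = 10.17.

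**Reproducing the plan's figure.** The non-centrality is N·f²/(1 − R²) = 208 × 0.172²/0.75 = 8.20. The non-central F distribution with 1 numerator df gives 81.4%; the normal approximation gives 81.7%. The stated 81% is reproduced as a two-sided test. A one-sided 5% test would give 88.9%, which does not match.

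**Variance of each contrast.** In units of the follow-up variance per patient, with equal SDs at baseline and follow-up:
- raw difference at a visit: 1
- change from baseline: 2(1 − r)
- baseline-adjusted (ANCOVA, or a common baseline mean): 1 − r²

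The standard error is 10.17 × √v × √(4/208), where v is the variance above.

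**At r = 0.5.**
- Raw or change: v = 1.00, SE = 1.41, power 69.5% (normal approximation 69.9%).
- Baseline-adjusted: v = 0.75, SE = 1.22, power 81.4% (81.7%).
- The ratio of standard errors is √(1/0.75) = 1.15.

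A generalised least squares calculation for all five visits, with a common correlation of 0.5, gives the same standard errors. With treatment free at baseline, both forms of the day-90 contrast have SE 1.411. With the arms constrained equal at baseline, SE is 1.222. In 4,000 simulated trials the rejection rates were 68.0% (raw), 68.8% (change) and 79.7% (ANCOVA).

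**Over the article's own correlations** (non-central F, 3.5 points, N = 208):

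| r | Raw visit difference | Change contrast | Baseline-adjusted |
|---|---|---|---|
| 0.39 | 69.5% | 60.8% | 76.5% |
| 0.50 | 69.5% | 69.5% | 81.4% |
| 0.57 | 69.5% | 75.9% | 85.2% |
| 0.70 | 69.5% | 89.0% | 93.3% |

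The normal approximation is 0.2 to 0.4 points higher throughout.

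**Unequal SDs.** The article gives no baseline SD. Let k be the ratio of baseline to follow-up SD. The change variance is then 1 + k² − 2rk, while the adjusted variance stays 1 − r². At r = 0.5, against 81.4% adjusted:
- k = 0.7: v = 0.79, power 79.3%
- k = 0.8: v = 0.84, power 76.8%
- k = 1.0: v = 1.00, power 69.5%
- k = 1.1: v = 1.11, power 64.9%

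**The case against.** The strongest reply is that nothing here is invalid. A longitudinal model with baseline as a response is an accepted analysis, and the mid-term tests run only after the primary endpoint has succeeded. That stands, and it limits the point to efficiency in a secondary analysis.

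The size of the loss is also uncertain. It depends on a baseline SD that the article does not give, on a pre/post correlation carried forward to day 90, and on complete data. With missing visits, the model still draws on baseline through the covariance, so the exact loss will differ. The tested contrast may be settled in an analysis plan that is not shown. Even so, the model as published contains no baseline constraint.

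A reader might infer four stronger things, which the document does not support:

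- **That the trial's stated power falls from 81% to about 70%.** The 81% belongs to the day-14 ANCOVA, which does adjust for baseline. No power or planned difference is given for days 28, 56 or 90.
- **That the mixed model targets a different treatment effect.** Under randomisation the change contrast and the baseline-adjusted difference estimate the same quantity.
- **That the model breaks down because baseline CAARS is both outcome and covariate.** A common slope of 1 would then fit the baseline visit exactly and the likelihood would be unbounded. But the Abstract calls the covariates categorical. That fits ADHD subtype and medication status, not a continuous score, and no common slope is stated.
- **That leaving out visit 5 and day 7 is a defect.** With complete data, a free mean for each arm and visit, and an unstructured covariance, adding them leaves the later contrasts unchanged.

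**Conclusion.** The point holds as a loss of precision and should be fixed; it is not a threat to validity. As published, the mid-term model gives day 28, 56 and 90 contrasts that are unbiased with correct type I error. They are nevertheless less precise than a baseline-adjusted contrast would be.

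Under equal SDs, complete data, a 3.5-point difference and 208 patients, the standard error at r = 0.5 is 15% larger and power is about 12 points lower. For the change contrast, the loss runs from about 16 points at r = 0.39 to about 4 points at r = 0.7. At r = 0.5 it shrinks to about 5 points if the baseline SD is 0.8 of the follow-up SD, and to about 2 points at 0.7. If the raw visit difference is tested instead, power stays near 70% whatever the correlation.

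**What to change.** Choose one of two forms and state it in the analysis plan:

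1. Model only days 14, 28, 56 and 90 as outcomes. Enter baseline CAARS as a continuous covariate with a baseline-by-visit term, plus the stratification factors.
2. Keep baseline as an outcome, constrain both arms to a common baseline mean, and do not also enter baseline as a covariate.

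In either case, name the baseline-adjusted treatment difference at days 28, 56 and 90 as the tested contrast, in the hierarchical order. With complete data, the two forms give essentially the same precision. The cost is a sentence or two, with no new data or visits and no change to the primary analysis or the sample size. It should be settled before unblinding.
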